**METHODS**

**Design**

This will be a double-blind sham-controlled two-arm randomized clinical trial. Fifty participants will be randomized (1:1) to each arm. Arm 1 will be active tDCS plus varenicline (n=25) and Arm 2 will be sham tDCS plus varenicline (n=25). Treatment duration will be 12 weeks. Subjects will be required to attend an in person assessment visit. They will then be randomized to a condition. Neuroimaging scans (fMRI) and eye-tracking tests will be conducted in all participants at baseline. Participants will undergo two scans at baseline on different days within the same week: one in a satiated state and one in a non-satiated state. The same tasks will be performed at each scan. s. Following the baseline fMRI scans and eye-tracking tests, subjects will start taking the varenicline simultaneous with starting the tDCS regimen whereby they will come to the clinic every day (Monday to Friday) for the first 2 weeks to undergo the stimulation (active: 20 minutes at 2mA, sham: 30 seconds at 2mA and then nothing). Their target quit date will be at the end of this 2 week period. They will return to the clinic every two weeks for the next 10 weeks for a booster tDCS session and to complete questionnaires. Eye tracking tests will be conducted at the end of the fourth and eighth weeks. At the end of the 12-week treatment period they will undergo a third fMRI scan and eye-tracking tests. For the next 14 weeks they will be contacted weekly by e-mail or text message to report on their smoking status as measured by the 7 day point prevalence abstinence question. “Have you had a cigarette, even a puff, in the last 7 days?” At the 6-month time point subjects will be asked to return to the clinic for a brief visit to confirm smoking abstinence using expired CO and urinary cotinine and to complete questionnaires.

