**Outcome Measures**

The primary outcome measure will be continuous abstinence from smoking during weeks 9 – 12 as reported at clinic visits during those 4 weeks and confirmed using expired CO. Subjects will be classified as treatment responders if they respond “no” to the question: Have you smoked any cigarettes (even a puff) in the last seven days?

The key secondary outcome measures are:

1. Self-reported 7 day point prevalence abstinence throughout weeks 2 to 12 confirmed by expired CO at each clinic visit. To calculate survival curves we will also collect self-reported continuous abstinence weeks 9 through 26. For weeks 13 to 25, this will be collected via email or text message. For week 26, subjects will attend a brief clinic visit so abstinence can be confirmed with expired CO and urinary cotinine using a semi-quantitative dipstick. We hypothesize that the active tDCS group will have higher rates of abstinence (less relapse) than the sham tDCS group.

2. fMRI: change in Blood Oxygen Level Dependent (BOLD) activation in brain regions known to be associated with drug craving and emotion processing/regulation. MRS: GSH levels measured in a single voxel placed over prefrontal cortex. Fractional anisotropy (FA) values will be extracted from DTI analysis from regions of interest (ROIs) or to form probabilistic tractography for the whole brain. Network maps will be extracted and analyzed from the resting state functional connectivity measure.

3. Eye Tracking tests: changes in attentional bias to smoking-related cues and negative emotional cues. Attentional bias to high-arousal/high-risk cues.

*Self-Report Measures*

Participants will complete the 10-item Questionnaire of Smoking Urges-Brief (QSU-10; Tiffany and Drobes, 1991) and the Minnesota Nicotine Withdrawal Scale (MNSW; Toll et al, 2007) at each treatment session upon arrival and immediately after tDCS. They will complete a Side Effects Checklist ([name] et al., 1995) at the end of each treatment session.

Trait scales to be completed at baseline will include the FTND (Heatherton et al 1991) and Alcohol Use Disorders Identification Test (Saunders et al., 1993), 90-day Alcohol Timeline Followback (TLFB; Sobell and Sobell, 1992); 30-day Tobacco Timeline Followback (adapted from alcohol TLFB); Sensation Seeking Scale (Zuckerman et al., 1978).

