**Data Analysis**

Continuous data (cravings, mood, cigarettes smoked/day, CO) will be assessed with 2 Gender x 2 (Laterality) x 10 (session) Analyses of Variance (ANOVA). Parallel ANOVAs will assess self-report measures during post-treatment follow-up. Categorical data (e.g., # abstinent participants/session) will be assessed with chi-square, and Kaplan-Meyer survival analysis for repeated measures. Planned comparisons will be performed for the critical experimental conditions (active tDCS) vs. sham.

The critical metric will be Effect Size (partial η2 generated by SPSS), rather than p level. This will reveal the degree of efficacy for the primary outcome variable, Consecutive Days Abstinent (small = .01, medium = .06, large = .14), and allow us to estimate N required to achieve statistical significance for this effect (80% power, α = .05, two-tailed). Pearson correlations will explore the possible relationship between effects of tDCS (session 10 scores, controlling for session 1) and trait factors (e.g., FTND, age, gender, depression).Analysis of MRI data

For the neuroimaging data, brain imaging measures will be compared between groups and across time points, using analysis of variance. MRI measures will also be related to subjective responses (i.e., baseline scores and changes in craving, mood, and withdrawal) using linear regression.

fMRI data will be analyzed by fitting a general linear model (GLM) to the data time-series at every voxel across the brain (and/or within ROIs) and assessing effects using F/t-tests and % signal change calculations. Quantitative T1 maps and DTI analysis will be analyzed at the whole brain level and using ROIs.

After back-sorting by treatment outcome (achieved/maintained abstinence), we expect baseline measures to predict relapse, and active tDCS treatment to result in more efficient functional activation, . than sham tDCS at the second MRI scan.

Analysis of Eye-Tracking Data

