For the eye-tracking data, gaze position data are processed by VAST into sequences of fixations and saccades and summary statistics of visual scanning parameters are computed. The VAST parameters include: the number of fixations, the average fixation duration, the average saccadic amplitude and the number of transitions for each image type. These parameters are sensitive measures of attentional bias for different visual cues. The outcome measures of this paradigm will be analyzed using a mixed-model analysis of variance (ANOVA). The within-groups factors are the image types (smoking, neutral, high valence) and session (sessions 1, 2, 3,4 and 5) and the between-groups factor is group (active tDCS and sham tDCS). Pearson’s product–moment correlations will be conducted between parameters of attentional bias and subjective craving scores. Through analysis, we will investigate and compare the treatment effects of varenicline and active tDCS on attentional bias in different sessions. We will also examine the relationship between changes in attentional bias and craving.

By means of a mixed design repeated-measures ANOVA, the VAST parameters will be compared within-subjects at 5 sessions to investigate the effects of varenicline treatment. The parameters will also be compared between the two groups of subjects to examine the treatment effects of active tDCS. We will also compare the VSB parameters of those who quit smoking in the last 4 weeks of treatment and those who were unable to remain abstinent to find out the possible indicators of treatment outcome. Pearson correlation method will be used to explore the relationships between: a) subjective craving and VSB parameters, b) sensation seeking behavior as measured by the sensation seeking scale measures and VSB parameters. Also we will use recurrent neural networks (Chung et al, 2018) to analyze differences between fixation sequences of patients that were treated with tDCS and patients that were not, and between patients that quit smoking and those that were not. Using Cox regression of survival analysis, we will also investigate the correlation between the length of abstinence (time to relapse) and VSB parameters associated with smoking cues, negative emotional cues and high-arousal/high-risk cues.

All data analysis will be conducted using SPSS, SPM or R as appropriate.

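### After week 12, continuous abstinence is built from weekly messages that ask only about the last 7 days, so a missed reply leaves a week that no named later assessment can confirm as smoke-free

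*Protocol*

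**What the plan says.** Under Outcome Measures, key secondary outcome 1 sets the record to be collected: "To calculate survival curves we will also collect self-reported continuous abstinence weeks 9 through 26". For the post-treatment part it adds: "For weeks 13 to 25, this will be collected via email or text message". That is 13 weekly contacts, followed by a clinic visit in week 26.

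The Design section describes the same period differently: "For the next 14 weeks they will be contacted weekly by e-mail or text message to report on their smoking status". It fixes the question: "Have you had a cigarette, even a puff, in the last 7 days". At 6 months participants return "to confirm smoking abstinence using expired CO and urinary cotinine and to complete questionnaires"; the questionnaires are not named. The Tobacco Timeline Followback, which could date past smoking, appears under Outcome Measures only among the scales completed at baseline.

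Data Analysis names "Kaplan-Meyer survival analysis for repeated measures" and plans a Cox regression for "the correlation between the length of abstinence (time to relapse) and VSB parameters". It gives no rule for unanswered messages. Such a rule is commonly left to the statistical analysis plan, so its absence is not part of this point.

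**The concern.** Continuous abstinence needs every week covered. A weekly question with a fixed 7-day window achieves that only if every message is answered. After a miss, the next message looks back over the following 7 days, and the missed week falls between the two. A participant who smoked in that week and then stopped again gives the same replies as one who never smoked. A participant who relapsed in that week and kept smoking is found later, but the relapse date is known only to lie within an interval.

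The length of abstinence feeds the survival curves, the Cox regression and the part of research question 1 about resistance to relapse in the long term. The defect lies in collection and has to be put right before the first follow-up message goes out. Misses are plausible: the compensation section lists payments for the assessment, the tDCS visits, the scans and the 6-month visit, but none for answering messages.

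**Working it through.** **Plan's own figure.** There is none on this point: the protocol states no expected reply rate and no expected long-term abstinence. Its only sample-size calculation, 25 per arm for 40% against 80%, does not bear on it.

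**Inputs**
- Messages: 13, for weeks 13 to 25 (Outcome Measures).
- Abstinent at week 12: 40%. This is the protocol's sham-arm assumption at end of treatment (Sample Size and Power Calculation), applied here to all 50, which gives 20 participants.
- Assumed: half of these stay abstinent over the 14 weeks to week 26, with constant weekly risk; relapse persists once begun; each message is answered independently with probability r, taken as 0.98, 0.95 or 0.90.

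**Step 1, weekly relapse risk.** h = 1 − 0.5^(1/14) = 0.0483.

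**Step 2, which misses matter.** A miss after a reported relapse is harmless. A participant who relapses in message week t is therefore gap-free if the first t messages are answered (probability r^t). One who does not relapse in the 13 weeks needs all 13 answered (r^13). With a = r(1 − h):

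P(no gap) = Σ (t = 1 to 13) h(1 − h)^(t−1) r^t + (1 − h)^13 r^13 = hr(1 − a^13)/(1 − a) + a^13

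| r | first term | a^13 | gap, of those abstinent at week 12 | × 0.40 = gap, of all participants |
|---|---|---|---|---|
| 0.98 | 0.419 | 0.404 | 18% | 7% |
| 0.95 | 0.350 | 0.270 | 38% | 15% |
| 0.90 | 0.263 | 0.134 | 60% | 24% |

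Out of 20 participants abstinent at week 12, this is about 4, 8 or 12. If the 14 weeks in the Design section mean 14 messages, the same formula with 14 in place of 13 gives 19%, 39% and 62%.

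**Step 3, gaps that no later yes resolves.** Suppose everyone attends at week 26. Persistent relapsers are then eventually found, and what remains are true abstainers with a missed week: 0.40 × 0.50 × (1 − r^13). This is 0.20 × 0.487 = 10% of all participants at r = 0.95 and 0.20 × 0.746 = 15% at r = 0.90.

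**Step 4, effect on the curve if gaps were censored at the first miss.** This used a simulation of 400,000 participants abstinent at week 12, with true week-26 abstinence of 50%, 14 weekly observations including the visit, and persistent relapse.

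| Reply rate while abstinent | Reply rate after relapse | Kaplan-Meier at week 26 |
|---|---|---|
| 0.95 | 0.95 | 50.0% |
| 0.95 | 0.80 | 55.5% |
| 0.95 | 0.60 | 64.4% |
| 0.90 | 0.50 | 67.5% |
| 0.80 | 0.95 | 44.0% |

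The bias is zero at equal reply rates, upward if relapsers reply less, and downward if abstainers reply less.

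**Step 5, two other rules in the same simulation.** Bridging gaps and placing relapse at the first yes gives 51.8% at reply rates of 0.95 and 0.60. Counting any missed reply as smoking gives 24.3% when both groups reply at 0.95 and 11.4% at 0.90.

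**The case against.** A reader might infer that non-repliers are censored and that the curve therefore overstates long-term abstinence. The protocol does not support this. It names Kaplan-Meier but never says how a non-reply is treated, and step 4 shows that even under censoring the direction depends on who stops replying. That part of the objection stands in full.

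A reader might also take 1 − r^13 (23%, 49% and 75% at the three reply rates) as the share of participants affected. That overcounts: it includes people who were not abstinent at week 12 and misses after a known relapse. The figures in step 2 replace it.

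Nor is every gap fatal. A later yes still shows relapse by that date, and the unnamed week-26 questionnaires could include recall. Bridging gaps nearly removes the bias in step 5, but only because relapse is assumed to persist. A lapse confined to a missed week would stay invisible, and the outcome counts even a puff.

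Finally, the curve is not the only long-term outcome. Abstinence at week 26 is confirmed by CO and cotinine independently of the messages. This is also a secondary outcome in a 50-person pilot that does not expect a significant difference. These points limit the weight of the concern, but the missed week remains unrecoverable by any assessment the protocol names.

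**Conclusion.** The point holds as a defect of data collection. With a fixed 7-day window, a missed reply leaves a week that no named later assessment can confirm as abstinent, and no analysis rule can supply the answer afterwards. Under the stated assumptions, about 18%, 38% or 60% of those abstinent at week 12 would have such a gap before any known relapse at 98%, 95% or 90% weekly replies. The reply rates are assumptions, since the protocol gives none.

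The consequence is uncertain relapse timing. Long-term abstinence would be overstated only if gaps were censored and relapsers replied less often than abstainers; the opposite reply pattern reverses the direction. The working gives no figure for the contrast between active and sham, which depends on whether reply patterns differ by arm. The weight is moderate: a key secondary outcome, with a cheap remedy that has to be in place before follow-up begins.

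**What to change.** 1. Keep the 7-day question, which preserves the weekly point-prevalence measure, and add to each message: *Since your last reply on [date], have you smoked, even a puff, and if so on what date?* Any later reply then fills the gap.
2. At the week-26 visit, ask the same back to the last reply of anyone with missed weeks, for example by extending the Tobacco Timeline Followback already used at baseline.
3. Reconcile the contact period: 14 weeks of messages in Design against weeks 13 to 25 in Outcome Measures. If the fourteenth week is the week-26 visit, say so.

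Handling of the gaps that remain belongs in the analysis plan, with a sensitivity analysis. A blanket rule that counts every unanswered week as relapse is not recommended here, because step 5 shows how far it can understate abstinence.

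The cost is slightly longer messages, plus some recall time and recall error at week 26.

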**Procedures**

Following the initial assessment appointment to obtain consent and confirm eligibility, the first tDCS treatment session will be booked. A breathalyser will screen for alcohol and expired CO at each tDCS session. The tDCS stimulation will take place in a quiet room, free of distractions. Stimulation will continue uninterrupted for 20 minutes with the experimenter in the room. While being stimulated, subjects will be required to read self-help materials related to smoking cessation, relapse prevention, and mood management. The readings for each day of stimulation will be standardized for all subjects.

To increase the opportunity to detect an acute beneficial effect of tDCS, participants will be asked to refrain from smoking for 2 hours prior to the start of each treatment session. Relative CO readings from the first day (ad lib smoking) compared to subsequent days will provide a coarse means of verifying compliance with the 2-hour pre-session smoke-free requirement.

Participants will be randomly assigned (1:1) to one of 2 treatment arms (double-blind). Participants will be matched as closely as possible on age, gender and cigarettes per day.

There will be 10 consecutive daily sessions of tDCS with the anode over the left DLPFC and cathode over the right DLPFC (active or sham) (Monday-Friday for 2 weeks; 2 mA x 20 min). Participants assigned to sham will have electrodes placed identically to active but receive only 30 seconds active stimulation. Participants will also be videotaped during each tDCS session to ensure consistency of tDCS application between research personnel and for documenting participant reactions during the session. This will also be used to document any side effects/complications participants may experience during the session. Each video tape session, as well as all data collected in the trial, will be stored on a secure server and will be retained for 10 years after the participant completes the study, as suggested by CAMH’s policy on Storage of Records. After each tDCS session, the video footage will be transferred from the camera to the secure server.

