**Management of Adverse Events (AE) and Serious Adverse Events (SAE)**

Side Effects in a study examining the side effects of 567 sessions of tDCS (Poreisz et al. 2007) with 77 healthy controls and 25 patients, tDCS was associated with a mild tingling sensation (70.6%) as well as moderate fatigue (35.3%) and a light itching sensation under the stimulation electrodes (30.4%). After tDCS, a headache (11.8%), nausea (2.9%) and insomnia (0.98%). 21.6% of volunteers experienced a slight burning (1.59±0.91) and 15.7% experienced a mild pain sensation (1.41±0.71) under the electrodes during the stimulation. 17.7% of the volunteers experienced tDCS as mildly unpleasant. The most common side effects of varenicline are nausea, abnormal dreams, constipation, flatulence and vomiting in 30, 13, 8, 6 and 5% of users, respectively. They are reversible and usually not severe. It is not known whether combining the two treatments will increase either the incidence or the severity of adverse effects, especially those that are common between the two treatments such as nausea and headache.

If a participant experiences an adverse event that requires hospitalization or results in lasting harm or death (SAE) and can reasonably be attributed to tDCS stimulation, the trial will be immediately suspended. Adverse events that can be expected based on the known profile of tDCS side effects will be managed by the Qualified Investigator ([name]). Depending on the severity of the unexpected adverse event, the Qualified Investigator will decide if the trial should be suspended. All SAEs, AEs and UAEs will be reported to the CAMH Research Ethics Board. The emergency contact for reporting SAEs is the Qualified Investigator ([name]).

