**Participant compensation**

Participants will be compensated as follow: $20 for baseline assessment (1), $20 per tDCS visit (15 total sessions), $95 per fMRI scans (3 sessions total) and $50 for 6 month follow up visit (1).

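### The Side Effects Checklist is given only at session end, with no pre-treatment or on-arrival form and no stated recall window, so symptoms cannot be attributed within a person and capture of delayed effects is not assured

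*Protocol*

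**What the plan says.** The Self-Report Measures part of Outcome Measures sets two timings in adjacent sentences. The craving and withdrawal scales are completed "at each treatment session upon arrival and immediately after tDCS". The next sentence deals with side effects: "They will complete a Side Effects Checklist ([name] et al., 1995) at the end of each treatment session". It gives no other administration and does not say what period the form asks about.

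Under Design, "subjects will start taking the varenicline simultaneous with starting the tDCS regimen", so the first checklist follows exposure to both treatments.

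The section on managing adverse events lists effects that come after stimulation, in per cent: "After tDCS, a headache (11.8%), nausea (2.9%) and insomnia (0.98". It gives varenicline nausea as 30% of users. It then says it is unknown whether the combination raises the incidence or severity of shared effects, naming nausea and headache. Background and Rationale names safety, beside efficacy, as something the sponsor hopes to show.

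Two other provisions bear on safety capture. Each session is videotaped, and Procedures says of the video: "This will also be used to document any side effects/complications participants may experience during the session". Adverse events of all kinds are to be reported to the ethics board, but no schedule for asking about them is given.

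**The concern.** A single form at the end of a session has to serve three purposes: recording what the participant arrived with, what happened since the last visit, and what the stimulation just caused. Without an earlier reading on the same day, these cannot be told apart. Without a reading before any treatment, symptoms that the participant already had cannot be told apart from treatment effects.

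At stake is the question the protocol itself raises, whether adding tDCS to varenicline increases nausea and headache. The values have to be collected at the visits; no later analysis plan can recover them. The craving and withdrawal scales already have a before-and-after schedule at the same visits, so the gap is specific to side effects.

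**Working it through.** **1. Number of checklists.** Procedures: "There will be 10 consecutive daily sessions of tDCS". Design: "They will return to the clinic every two weeks for the next 10 weeks for a booster tDCS session and to complete questionnaires". That is 10 + 10/2 = 15 sessions. Participant compensation agrees: "20 per tDCS visit (15 total sessions". So there are 15 checklists per participant, all at session end.

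**2. Spacing.** The treatment period is 12 × 7 = 84 days. Checklists fall on 15/84 = 18% of days overall and on 5/70 = 7% of days in weeks 3 to 12. The gap is a day or a weekend in weeks 1 and 2, and about 14 days afterwards.

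**3. The recall window, taken both ways.**
- If the form covers the session only, insomnia or a headache that begins later is not asked about at any scheduled point.
- If it covers the time since the last visit, one form merges symptoms present on arrival, symptoms that came and went in the interval, and symptoms caused by the session.

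On either reading no checklist follows session 15. The weekly contacts after treatment ask about smoking status, and the 6-month questionnaires are not named.

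**4. Where the rates come from.** The tDCS series has 77 + 25 = 102 people. The figures fit counts of 12/102 = 11.8%, 3/102 = 2.9% and 1/102 = 0.98%, so they look like per-person proportions from small counts. The varenicline rate is per user over an unstated period. Neither is a prevalence at a visit, so what follows is an illustration over a range. Headache cannot be illustrated, because no varenicline headache rate is given.

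**5. Nausea with the end-of-session form only.** Let v be varenicline nausea at a visit (assumed 10%, 20% or 30%) and t = 2.9% tDCS nausea, assumed independent, with none caused by sham. The sham arm reports v. The active arm reports a = 1 − (1 − v)(1 − t). The share of active-arm reporters with varenicline nausea is v/a. Power is the chance of a significant result in the right direction, Φ[(a − v − 1.96·SE₀)/SE₁], with n = 25 per arm and two-sided 5%; SE₀ and SE₁ are the pooled and unpooled standard errors.

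| v | a | a − v | v/a | power |
|---|---|---|---|---|
| 10% | 12.6% | 2.6 points | 79% | 4.7% |
| 20% | 22.3% | 2.3 points | 90% | 3.9% |
| 30% | 32.0% | 2.0 points | 94% | 3.6% |

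**6. What an arrival form could remove, at best.** Suppose all varenicline nausea seen at session end was already there on arrival. New onset during the session is then (1 − v)t in the active arm and 0 on sham: the same 2.0 to 2.6 points, without the background.
- At v = 30%, the standard error of the difference falls from √(0.30×0.70/25 + 0.3203×0.6797/25) = 0.131 to √(0.0203×0.9797/25) = 0.028.
- At v = 10%, it falls from √(0.10×0.90/25 + 0.1261×0.8739/25) = 0.089 to √(0.0261×0.9739/25) = 0.032.

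The expected number of such events is still only 25 × 0.0203 = 0.5 to 25 × 0.0261 = 0.65, so this supports description, not a test.

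**The case against.** A reader might infer that effects arising after or between sessions are lost. The documents do not show this. They state when the form is completed, not the period it covers, and the instrument itself is not reproduced. A form at the end of one session may record the previous night's insomnia, and in weeks 1 and 2 the next form is at most a weekend away. All adverse events are also to be reported, without restriction to sessions. This objection stands: the supportable statement is that capture of delayed effects is not assured.

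A reader might also infer that varenicline effects hide or distort the difference between arms. That is not supported either. Both arms take varenicline under randomisation, blinding and sham control, and complete the same form at the same time, so the expected background is equal and the contrast is unbiased. The main limit on precision is 25 per arm, which the fix does not change.

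Third, side effects are not among the listed primary or key secondary outcomes. The suspension rule concerns hospitalisation, lasting harm or death, which would not be judged mainly from a symptom form. This also stands, and it keeps the point modest.

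None of this supplies a pre-treatment value, an arrival value or a recall window. The video covers only the session, and the general reporting duty has no schedule for asking.

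**Conclusion.** The point holds as a limitation of the side-effect schedule. With forms at session end only, both treatments starting together and no recall window, a reported symptom cannot be divided within a person into one present before treatment, one that arose between sessions (varenicline or delayed tDCS) and one induced by the session. The trial can compare arms without bias, but with avoidable noise, and it can say less than it could about shared effects such as nausea and headache.

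The size is illustrative: 79% to 94% of active-arm nausea reporters would have varenicline nausea at visit prevalences of 10% to 30%. This rests on independence, no nausea from sham, and rates taken from unlike sources. The schedule itself does not depend on those assumptions. This is a worthwhile, inexpensive improvement; it does not undermine the efficacy analysis.

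**What to change.** In Self-Report Measures, schedule the same checklist at three points and state the recall window for each:
- once before the first varenicline dose and the first tDCS session;
- on arrival at each session, alongside the QSU and the withdrawal scale, asking about the time since the last visit;
- at the end of each session as now, asking about that session only.

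Report by arm the end-minus-arrival change and, separately, the events since the last visit.

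This takes the count from 15 forms to 15 + 15 + 1 = 31 per participant, at visits that already exist. The downside is a few minutes of added burden at each of 15 visits. No sample-size figure changes. The arrival form does not reach the period after session 15. A form at the end-of-treatment scan would help only if that scan falls after the last session, and the protocol does not state the order.
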